### Outcome data

Genetic association data for CRC risk will be obtained from a GWAS meta-analysis of colorectal cancer in 78,473 cases and 107,143 controls
^
30
^. This study used data from several studies of individuals of European ancestry, including the Genetics and Epidemiology of Colorectal Cancer Consortium (GECCO), the Colorectal Transdisciplinary Study (CORECT), COloRectal cancer Study of Austria (CORSA) and UK Biobank. This GWAS was adjusted for age, sex and genetic principal components of ancestry (PCs). Details on participants, genotyping and quality control (QC) have been described previously
^
30
^. The summary data from this GWAS is available without UK Biobank data. Where there is sample overlap between the CRC GWAS and the exposure GWAS (i.e. those studies conducted exclusively in UK Biobank) and we have a significant finding from the main analyses after accounting for multiple testing (using a false discovery rate (FDR) correction of <5%), we will conduct a sensitivity analysis using CRC data with UK Biobank excluded. We will also compare the individual studies included in the CRC GWAS with all exposure datasets (i.e. beyond overlap of UK Biobank participants). Where there is a small-to-modest proportion of participant overlap between the studies included in the exposure data and the CRC data, we will quantify this overlap and, for any significant findings, we will repeat analyses using a more stringent F-statistic threshold (e.g.
31) to select genetic instruments. Sample overlap is only an issue if the genetic instruments used are weak
^
32,
33
^, therefore repeating analyses with a more stringent F-statistic threshold should minimise the likelihood of including weak instruments in analyses.

### Power

As we will be testing the effect of a number of different molecular traits on CRC risk, the phenotypic variance explained by the instruments (r
^2^) used for each trait will vary. We have therefore calculated
^
31
^ the statistical power of analyses for a range of r
^2^ values and odds ratios (
Figure 1).

**Figure 1. f1:**
[figure not shown]
Potential statistical power to detect an association between preventive therapy agents and CRC risk. Abbreviations: CRC = colorectal cancer. Statistical power to detect an association between preventive therapy agents and CRC risk was calculated for three effect estimates (odds ratio per standard deviation increase in risk factor) (0.7, 0.8, 0.9) and a range of r
^2^ values (0.001, 0.005, 0.01, 0.05) with 5% significance level and total sample size of 185616 (cases=78473, controls=107143).

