### Main analyses

The proportion of variance in the molecular traits explained by the SNPs used as instrumental variables (r
^2^) and the strength of the instrument (F-statistic) will be calculated. The F-statistic can be used to test the “relevance” assumption and a threshold of >10 indicates that weak instrument bias is unlikely
^
35
^.

The proportion of variance explained in the instruments (R2) will be calculated using the following formula: 

$$R^{2}=\frac{2\beta^{2}MAF(1-MAF)}{2\beta^{2}MAF(1-MAF)+{\left(se(\beta )\right)}^{2}(2N)MAF(1-MAF)}$$

Where β is the effect size (beta coefficient) for a given SNP, MAF is the minor allele frequency, se(β) is the standard error of the effect size, and N is the sample size. 

F-statistics will be calculated using the following formula:

$$F=R^{2}(N-2)/(1-R^{2})$$

Where R2 is the proportion of variance explained in the instrument, N is the sample size

For molecular traits instrumented by a single SNP, the Wald ratio will be used to calculate the effect of the molecular exposure on CRC risk
^
23
^. For those traits that are instrumented by more than one SNP, the inverse-variance weighted (IVW) method will be used
^
23
^. The multiplicative random effects IVW will be prioritised, except where the number of SNPs is limited (e.g. ≤3) in which case the fixed effects IVW will be used.

To account for multiple testing, we will use a false discovery rate (FDR) correction of <5% to define strong evidence.

We will attempt to explore analyses stratifying by cancer subsite (e.g. distal, proximal, colon, and rectal). This will require requesting access for restricted GWAS data
^
36
^.

We will explore conducting multi-variable MR (MVMR)
^
37
^ for significant findings (reaching an FDR corrected threshold of <5%) for which there is genetic overlap between instruments. We will use MVMR when we suspect this genetic overlap is more likely to reflect horizontal, as opposed to vertical, pleiotropy.

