## Study status

At the time of submission of this protocol for publication, preventive agents have been identified from the literature and we have identified the corresponding molecular trait for each agent. We have determined which molecular traits are instrumentable and, for those that are (
Table 2), we have begun to identify genetic instruments.

**Table 2. T2:** Preventive agents identified in the literature to be associated with CRC risk reduction.

Preventive agent	Molecular trait
Dietary long-chain omega-3 polyunsaturated fatty acids	Circulating long-chain omega-3 polyunsaturated fatty acids
Dietary long-chain omega-6 polyunsaturated fatty acids	Circulating long-chain omega-6 polyunsaturated fatty acids
Dietary salicylic acid	Plasma salicylic acid levels
Dietary calcium	Serum calcium levels
Dietary vitamin D	Serum 25 hydroxyvitamin D
Dietary folate levels	Serum folate levels
Dietary selenium	Circulating selenium levels
Dietary vitamin A	Serum retinol levels
Dietary vitamin C	Plasma vitamin C levels
Dietary vitamin E	Circulating alpha-tocopherol levels
Dietary β carotene	Circulating β carotene levels
Dietary magnesium	Serum magnesium levels
Statins	Circulating LDL cholesterol levels (due to HMG-CoA reductase inhibition)
Guselkumab	Plasma IL23 protein levels
Antihypertensives	Serum ACE levels
	SBP (due to NCC inhibition)
	SBP (due to ADRB1 inhibition)
Testosterone	Circulating testosterone levels
Estradiol	Serum estradiol levels
Sex hormone binding globulin	Serum SHBG levels
Progesterone/17- hydroxyprogesterone	Circulating progesterone/17- hydroxyprogesterone levels

Abbreviations: CRC = colorectal cancer; LDL = low-density lipoprotein; HMG-CoA = 3-hydroxy-3-methylglutaryl coenzyme A; IL23 = interleukin 23; ACE = angiotensin-converting enzyme; SBP = systolic blood pressure; NCC = sodium chloride cotransporter; ADRB1 = β1 adrenoceptor; SHBG = sex hormone binding globulin. Preventive agents identified in the literature that had a corresponding molecular trait that was deemed instrumentable. These agents included dietary micronutrients, drugs and endogenous hormones. For each drug, the biological target of the drug was identified as it’s molecular trait, (e.g. the levels of the protein that the drug targets). For dietary micronutrients and endogenous hormones, molecular traits were identified that correspond to the agent (e.g. blood-based biomarkers for vitamin levels).

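### Figure 1 gives power at an unadjusted 5% level, but findings are declared at FDR <5% over about 21 traits, so it overstates power for the plan's own rule

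*Protocol article*

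**What the plan says.** The Figure 1 caption in the protocol article gives the inputs to the power calculation: "three effect estimates (odds ratio per standard deviation increase in risk factor) (0.7, 0.8, 0.9"), instrument r2 "values (0.001, 0.005, 0.01, 0.05"), and a single test "with 5% significance level and total sample size of 185616 (cases=78473, controls=107143"), which is the full colorectal cancer sample. It mentions no adjustment for multiplicity and does not state sidedness. The Power section notes that several traits will be tested, but takes from this only that r2 will differ between them.

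The Main analyses section sets the decision rule: "To account for multiple testing, we will use a false discovery rate (FDR) correction of <5% to define strong evidence". The same section reserves multivariable MR for "significant findings (reaching an FDR corrected threshold of <5"%). An FDR-significant result is also what triggers the analysis without UK Biobank (Outcome data) and Steiger filtering (Sensitivity analyses).

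Table 2 under Study status lists the traits to be tested, described as "Preventive agents identified in the literature that had a corresponding molecular trait that was deemed instrumentable". It has 21 trait rows: 12 dietary, 1 statin, 1 guselkumab, 3 antihypertensive and 4 hormone.

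**The concern.** The level used for power and the level used to declare a finding are both stated in the article, and they differ. With 21 tests, Benjamini-Hochberg compares the R-th smallest p-value with 0.05 × R/21. The threshold is therefore 0.0024 if one trait is flagged, and 0.05 only if all 21 are.

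What is at stake is interpretation. The study screens candidate agents, so many results may be null. The power figure is the article's only statement of what the analysis can detect. If a null is read against a curve drawn at 5%, a trait with a weak or moderate instrument can look adequately tested when the FDR rule had a much smaller chance of flagging it.

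**Working it through.** **Inputs from the article.** The Outcome data section describes a "GWAS meta-analysis of colorectal cancer in 78,473 cases and 107,143 controls". The total is 78,473 + 107,143 = 185,616, which matches the caption. Case share p = 78,473/185,616 = 0.4228, so N·p·(1−p) = 45,297. The OR and r2 grid is from the caption, and the 21 trait rows are from Table 2.

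**Assumptions, not in the article.** Two-sided tests; Benjamini-Hochberg as the FDR procedure; one family of m = 21 (22 if progesterone and 17-hydroxyprogesterone are tested separately); independent tests; one or five true effects of equal size, the other traits null.

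**Formula.** The test statistic has mean λ = |ln OR| × √(r2 × 45,297). Power at two-sided level α is Φ(λ − z(1−α/2)), plus a negligible opposite tail. Here z = 1.960 at α = 0.05 and z = 3.038 at α = 0.05/21 = 0.00238.

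**The plan's own figure.** Figure 1 is not shown, so its plotted values cannot be compared. The 5% column below is what the caption's inputs give. A non-central chi-square version of the calculation agrees within 2 percentage points.

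**Worked cell, OR 0.8 and r2 0.005.** λ = 0.2231 × √226.5 = 3.358. At 5%: Φ(3.358 − 1.960) = 91.9%. At 0.05/21: Φ(3.358 − 3.038) = 62.6%.

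**Whole grid.** The last two columns are simulated Benjamini-Hochberg power at 5%, m = 21.

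| r2 | OR | Power at 5% | At 0.05/21 | BH, 1 true effect | BH, 5 true effects |
|---|---|---|---|---|---|
| 0.001 | 0.7 | 67.0% | 26.2% | 27% | 36% |
| 0.001 | 0.8 | 32.4% | 6.2% | 7% | 8% |
| 0.001 | 0.9 | 10.9% | 1.0% | 1% | 1% |
| 0.005 | 0.7 | >99.9% | 99.0% | 99% | 99.8% |
| 0.005 | 0.8 | 91.9% | 62.6% | 63% | 78% |
| 0.005 | 0.9 | 35.4% | 7.3% | 8% | 9% |
| 0.01 | 0.7 | 100% | 100% | 100% | 100% |
| 0.01 | 0.8 | 99.7% | 95.6% | 96% | 99% |
| 0.01 | 0.9 | 61.1% | 21.3% | 22% | 29.5% |
| 0.05 | 0.7 | 100% | 100% | 100% | 100% |
| 0.05 | 0.8 | 100% | 100% | 100% | 100% |
| 0.05 | 0.9 | 99.9% | 97.6% | 98% | 99% |

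With one true effect, power drops by about 26 to 40 points in five of the twelve cells, by about 10 points in one (OR 0.9, r2 0.001), and by less than 4 points in the other six.

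**Instrument strength needed for 80% power.** r2 = (z(1−α/2) + 0.842)² / (45,297 × (ln OR)²). From α = 0.05 to 0.05/21 this rises from 0.0014 to 0.0026 (OR 0.7), from 0.0035 to 0.0067 (OR 0.8), and from 0.0156 to 0.0299 (OR 0.9). At the bound, the r2 required is nearly doubled.

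**Sensitivity.** With m = 22 the bound moves by less than one point in every cell. If the caption's 5% were one-sided, the gap would widen: OR 0.7 at r2 0.001 would show 77.5% instead of 67%.

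**The case against.** The caption states its 5% level openly, calls the result potential power, and does not claim to describe the FDR rule. The one sum that can be checked is right. The outcome dataset already exists, the article sets no power target, and no trait is included or dropped because of Figure 1. Changing the figure would alter no estimate and no FDR decision. The article also commits to reporting each instrument's r2 and F-statistic. Benjamini-Hochberg is adaptive, so 0.05/21 is a lower bound on the threshold and not the plan's rule.

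All of this stands, and it limits the weight of the point. It does not remove the mismatch: a power figure for a test the plan will not use to declare findings is a poor guide to what the plan can find.

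A reader might infer more than the documents support:

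- **That the plotted values are wrong.** The figure is not visible, so this cannot be shown. The problem is the level it is drawn at.
- **That agents will be dismissed as having no effect.** The article uses FDR to define strong evidence and nowhere says that a null is evidence of absence. The risk lies in how a reader may use the figure.
- **That the r2 grid stops too high at 0.001.** The article's formula allows a smaller r2 for a single barely significant SNP, but how small depends on exposure sample sizes that the article does not give. Instruments were still being identified.
- **That a fixed threshold of 0.25/21 gives FDR power with five true effects.** It treats five discoveries as certain. It gives 45%, 39% and 18% where simulation gives 36%, 29.5% and 9% (OR 0.7 at r2 0.001; OR 0.9 at r2 0.01; OR 0.9 at r2 0.005).

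**Conclusion.** The point holds as a should-fix. Figure 1 is drawn at a level that the plan's decision rule reaches only if every trait is rejected. Under Benjamini-Hochberg the direction does not depend on how many effects are real: FDR power cannot exceed power at an unadjusted 5%.

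The size does depend on that number, on independence, and on taking the 21 rows of Table 2 as the family, none of which the article fixes. Under those assumptions the overstatement is large for r2 of 0.001 to 0.005 with modest effects and for OR 0.9 at r2 0.01. The cell at OR 0.8 and r2 0.005 falls below the customary 80% even with five true effects. For stronger instruments the loss is negligible or a few points, and the figure remains a fair guide.

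The consequence is confined to reading null results. The documents do not support calling this a flaw that invalidates the analysis or must be cured before it can proceed.

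**What to change.** Recompute Figure 1 at a threshold consistent with the FDR rule. The simplest form keeps the 5% curve, labels it unadjusted, and adds a curve at 0.05/m as the lower bound, stating m and which tests make up the family. Simulated Benjamini-Hochberg power under stated numbers of true effects would serve equally well. A fixed 0.25/21 curve would not, since it overstates FDR power in several cells. State the sidedness and the FDR procedure in the caption. In the results, read each null against the restated figure at that trait's achieved r2, which the plan already undertakes to calculate.

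The cost is one calculation and one redrawn figure, with no new data and no change to the analysis. The stated power will look less favourable. Extending the r2 axis below 0.001 and reporting a minimum detectable OR for each trait are optional additions.

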### Data harmonisation

The summary statistics from the exposure and outcome data will be harmonised so that the effect allele of a particular SNP in the exposure dataset corresponds to the same allele of that same SNP in the outcome dataset. If alleles need to be switched in the outcome dataset, the effect estimate for the outcome will also be changed to reflect this. SNPs included in the harmonised data must therefore be present in both the exposure and outcome datasets.

Harmonisation will be carried out using the TwoSampleMR package in R (v0.5.8)
^
34
^. The harmonise_data function will be used with the default setting which uses allele frequencies to resolve palindromic SNPs (e.g. where the effect/non-effect allele are either A/T or G/C combinations). If it is not possible to resolve strand ambiguity for palindromic SNPs (i.e. the minor allele frequency is above 0.42) these SNPs will be excluded from subsequent analyses. To check that the harmonisation step has worked as expected, the correlation between effect allele frequencies in the exposure and outcome dataset will be calculated. A correlation close to 1 would indicate the data were successfully harmonised (and would also indicate that the exposure and outcome datasets are representative of the same underlying population, a key assumption of the two-sample MR approach).

### Mendelian randomization

**
*Assumptions*.** To provide a valid test of the causal null hypothesis, MR requires three instrumental variable (IV) assumptions to hold: “relevance”, “exchangeability”, “exclusion restriction”
^
20–
23
^. The “relevance” assumption states that the instrumental variable is strongly associated with the exposure of interest (e.g. a particular molecular trait being evaluated). The “exchangeability” assumption states there are no confounders (e.g. population structure) of the instrument and outcome. The “exclusion restriction” assumption states that the instrumental variable must only be associated with the outcome through the exposure (e.g. there is no horizontal pleiotropy, where the instrument influences the outcome through pathways independent of the exposure). Under the assumption of monotonicity, valid point estimates can be generated for those participants whose exposure is influenced by the instrument (i.e. a local average treatment effect).

### Main analyses

The proportion of variance in the molecular traits explained by the SNPs used as instrumental variables (r
^2^) and the strength of the instrument (F-statistic) will be calculated. The F-statistic can be used to test the “relevance” assumption and a threshold of >10 indicates that weak instrument bias is unlikely
^
35
^.

The proportion of variance explained in the instruments (R2) will be calculated using the following formula: 

$$R^{2}=\frac{2\beta^{2}MAF(1-MAF)}{2\beta^{2}MAF(1-MAF)+{\left(se(\beta )\right)}^{2}(2N)MAF(1-MAF)}$$

Where β is the effect size (beta coefficient) for a given SNP, MAF is the minor allele frequency, se(β) is the standard error of the effect size, and N is the sample size. 

F-statistics will be calculated using the following formula:

$$F=R^{2}(N-2)/(1-R^{2})$$

Where R2 is the proportion of variance explained in the instrument, N is the sample size

For molecular traits instrumented by a single SNP, the Wald ratio will be used to calculate the effect of the molecular exposure on CRC risk
^
23
^. For those traits that are instrumented by more than one SNP, the inverse-variance weighted (IVW) method will be used
^
23
^. The multiplicative random effects IVW will be prioritised, except where the number of SNPs is limited (e.g. ≤3) in which case the fixed effects IVW will be used.

To account for multiple testing, we will use a false discovery rate (FDR) correction of <5% to define strong evidence.

We will attempt to explore analyses stratifying by cancer subsite (e.g. distal, proximal, colon, and rectal). This will require requesting access for restricted GWAS data
^
36
^.

We will explore conducting multi-variable MR (MVMR)
^
37
^ for significant findings (reaching an FDR corrected threshold of <5%) for which there is genetic overlap between instruments. We will use MVMR when we suspect this genetic overlap is more likely to reflect horizontal, as opposed to vertical, pleiotropy.

### Sensitivity analyses

For instrumental variable sets that use more than one genetic instrument, the analyses will be iteratively repeated, each time leaving out one SNP to test if there is a particular SNP that is driving results, which could be due to the outlying SNP being the only valid instrument or due to this SNP being horizontally pleiotropic.

We will apply “pleiotropy-robust” models as sensitivity analyses when sufficient independent genetic instruments are available (e.g. ≥ 10), given low statistical power of these models. These models include the weighted median
^
38
^, weighted mode
^
39
^ and MR Egger
^
40
^ regression and effect estimates from these methods can be compared to the IVW estimate obtained in initial analyses to evaluate if observed effects are possibly driven by horizontal pleiotropy. The weighted median can provide an unbiased causal estimate even when some of the genetic instruments used are invalid, the weighted mode effect estimate is more robust to horizontal pleiotropy, and the MR-Egger regression intercept can provide an indication of directional (i.e. unbalanced) pleiotropy. Whilst these sensitivity analyses relax certain assumptions of the IVW method, these models introduce new assumptions, so it is therefore important to use all three methods for comparison. If a consistent effect is observed across these three methods and the IVW estimate obtained from the main analyses, it is less likely that this finding is driven by violations of MR assumptions. To support these findings we will also use MR-PRESSO
^
41
^ to detect, and correct for, horizontal pleiotropy. This method assumes the majority of SNPs used as instruments are valid. 

For any exposures found to be associated with CRC risk, after applying an FDR correction, Steiger filtering will be used to explore the causal direction of SNP effects
^
42
^. The steiger_filtering function in the TwoSampleMR package will be used to evaluate if findings are driven by reverse causation, whereby the SNP used to instrument a molecular trait has an effect on CRC which in turn impacts variation in the molecular trait.

### Colocalisation

To determine if there is a shared causal variant between putative preventive agents and CRC risk, which is a requirement for inference of a causal effect of an agent on CRC risk, colocalisation will be conducted using the ‘coloc’ package in R
^
43
^. The default parameters will be used (e.g. the prior probabilities of the SNP being associated with the exposure, the outcome or both traits is specified as 1×°10
^-4^, 1×°10
^-4^ and 1×°10
^-5^, respectively). As a sensitivity analysis we will use a more stringent threshold to test p12 (e.g. 1×°10
^-6^). Bayes factor computation will be used to generate posterior probabilities (H0–H4) for the following 5 relationships between traits: (H0) neither trait has a causal variant in the region; (H1) only the molecular trait of interest has a causal variant in the region; (H2) only CRC risk has a causal variant in the region; (H3) both traits have associations within the genomic region but have different causal variants and (H4) both traits have the same causal variant. The posterior probability with the majority of support out of all configurations (e.g. a threshold of >0.50) will be used to evaluate evidence of a shared causal variant between preventive agents and CRC risk. Given that the posterior probability of colocalisation is on a continuum, we will classify PPH4 of 50% to 100% as providing a continuum of evidence in favour of shared causal variants (e.g. PPH4 ~ 50–80% as suggestive evidence for colocalisation, >80% as strong evidence for colocalisation). Colocalisation analyses will also be run using a method that allows for multiple causal variants, such as SuSiE
^
44,
45
^, to compare with the coloc results. Regional association plots will be generated to visualise results of colocalisation at the genetic region of interest using the LocusCompareR package
^
46
^.

### Data and software availability

This analysis will use publicly available summary statistics of CRC risk (
https://www.ebi.ac.uk/gwas/studies/GCST90255675) and molecular traits (either obtained through the GWAS catalogue, the IEU Open GWAS or directly from the published GWAS). For subsite-stratified analyses, access to this data will be requested through GECCO.

We will use the TwoSample MR package (v0.5.8) for MR analyses (
https://mrcieu.github.io/TwoSampleMR/), the ‘coloc’ package (
https://chr1swallace.github.io/coloc/) and SuSiE (
https://stephenslab.github.io/susieR/) for colocalisation analyses, and the LocusCompareR package (
https://github.com/boxiangliu/locuscomparer) to visualise regional genetic association data used in colocalisation analyses. All packages will be used in R.

